### 5.2 Principles of analysis

171

172 The primary conclusions from this study will be based on analyses conducted under the principle of  
 173 intention-to-treat. Thus, all randomised patients, with exception to those who withdraw their  
 174 consent, will be included in the analyses. In the analysis, it is further assumed that all randomised  
 175 patients receive the treatment they were randomised to.

Those patients who are randomised but withdraw their consent to use their data will not be included in any analyses. Only the information that they were enrolled into the study and withdrew their consent, and the original treatment group to which they were allocated, will be reported.

Data from all operating clinics (centres) will be pooled in primary analyses. The study will be conducted under a common protocol for each participating clinic with the intention to pool the data for analyses.

In addition to the primary analysis using intention-to-treat population, exploratory analyses using per-protocol (as treated) populations will be conducted for all outcome variables.

For primary outcomes, two-sided 2.5% significance level will be used to identify statistically significant results. The corresponding confidence intervals to be reported will be 97.5% confidence intervals. The use of 2.5% significance is due to two primary endpoints.

There will not be any formal interim analyses on primary outcomes. The safety and Data Monitoring Committee has a responsibility to monitor adverse events and complications during the study follow-up period.

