### Primary outcome measure

To evaluate whether SG has advantages compared to previous standard GBP, we want to investigate whether the surgical methods are equivalent (non-inferiority) regarding weight loss and weight stability five years after the operation, and whether SG is associated with fewer long-term complications (superiority). The primary outcome measure is thus based on a balanced assessment of long-term weight control and the frequency of serious complications.

Serious complications (Substantial Adverse Events) are defined as:

- Death caused by complication of bariatric surgery.
- Intervention in general anesthesia (Clavien-Dindo 3b and higher) for complication to bariatric surgery. Among these, gallstone interventions, hernias that were present before the primary operation and plastic surgery due to excess skin are excluded. Subgroup analysis of negative laparoscopies is planned.
- Intensive care as a result of a complication to obesity surgery  
Revision surgery (change of surgical method, reversal or significant change of original method) Revision surgery is performed according to clinical practice. The indication for revision surgery, e.g. unsatisfactory weight development or possible occurrence of GERD must be documented.
- Hospital care for an operation-related complication (apart from observation less than 1 day)
- Need for enteral (via tube to the GI tract) or parenteral total/supplemental nutrition
- Chronic abdominal pain (> 6 months) that requires regular (several times per week or daily) medication of opiates (ATC code N02A, including Tramadol and

- Codeine) and/or abdominal pain that significantly affects daily life (prevents normal work, leisure activities, etc.)
- Frequent and severe meal-related problems that affect the normal way of life for at least 3 months (eg hypoglycaemia, pain, vomiting, nausea).
  - Hypoglycemia associated with loss of consciousness/convulsions or requiring drug treatment
  - Gastro-oesophageal reflux problems that cannot be controlled with medication (including volume reflux). Barrett's esophagus (in cases where you had a preoperative normal endoscopy within 2 years before the op).
  - Clinically relevant, symptomatic deficiencies of vitamins and/or minerals.
  - Severe anemia; Hb <100 g/L in women and <110 g/L in men.
  - Other serious complication that is not predefined but after assessment by the reference group is judged to be surgery-related

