## 2. Study objectives

The objective of the study is to evaluate the safety and effectiveness of SG compared to GBP in obese patients eligible for bariatric surgery.

The study has two primary objectives, evaluating superiority and non-inferiority. The study hypothesis for superiority is that patients treated with SG will experience fewer adverse events during the 5-year follow-up as compared to patients treated with GBP.

For non-inferiority, the study hypothesis is that the weight loss in the SG group, as compared to GBP, is within a non-inferiority margin of 5% at 5 years after surgery.

Secondary objectives of the study include health economics, inpatient hospital and outpatient care, drug consumption, alcohol abuse, fractures and bone quality, diabetes, cancer, mortality, and quality of life.

Predefined subgroup analyses will be done by sex, age, diabetes status and body mass index (BMI).

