## 4. Study outcomes

A list of substantial adverse events in bariatric surgery (tabl 2) was predefined before study start. Possible occurrence of any of these will be identified in the CRF (SOREg) but additionally from the national quality health care registries (listed above) during 5-years of follow-up. A superiority of SG over GBP would require >35% fewer patients experiencing one or more substantial adverse event.

Time to occurrence of first substantial adverse event will be analysed as the co-primary outcome. Patients will be defined as either having or not having an event, and thus the number of events in the same patients will not be summarized.

For non-inferiority, weight loss difference over 5-years in patients operated with SG as compared to GBP will be evaluated with regards to the non-inferiority margin of 5%.

Table 1: Primary outcomes:

| Outcome                    | Time frame                  | Explanation                                                                          |
|----------------------------|-----------------------------|--------------------------------------------------------------------------------------|
| Weight loss                | At 5 years after surgery    | Change in weight from baseline in % of total body weight                             |
| Substantial adverse events | Over 5 years after surgery. | Number of patients with any substantial adverse events defined according to table 2. |

Table 2: Substantial adverse events: (events that may have a significant and/or longstanding effect on patients' health and/or everyday life).

| Substantial adverse event              |                                                                                                                                                                                                                                                                                               |
|----------------------------------------|-----------------------------------------------------------------------------------------------------------------------------------------------------------------------------------------------------------------------------------------------------------------------------------------------|

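### The fixed two-sided 2.5% split across the two primary outcomes is valid, but Holm would give more power for the second outcome and for showing both, at the same family-wise 5%

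*Combined protocol and SAP*

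**What the plan says.** SAP section 2 states: "The study has two primary objectives, evaluating superiority and non-inferiority". Each objective has its own hypothesis: fewer substantial adverse events with SG over 5 years, and 5-year weight loss within a 5% margin of gastric bypass (GBP).

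On the level of testing, SAP 5.2 says: "For primary outcomes, two-sided 2.5% significance level will be used to identify statistically significant results". It adds "The corresponding confidence intervals to be reported will be 97.5% confidence intervals" and explains that "The use of 2.5% significance is due to two primary endpoints". SAP 5.3 decides non-inferiority by setting the confidence interval for the weight-loss difference against the margin, so the interval level is also the decision level.

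The relation between the two outcomes is described in two other places. SAP section 4 says: "Time to occurrence of first substantial adverse event will be analysed as the co-primary outcome". The protocol, under Primary outcome measure, speaks of a "balanced assessment of long-term weight control and the frequency of serious complications". Neither attaches a rule. No section says whether success needs both outcomes or either, or what is concluded overall if they disagree.

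The SAP appendix gives the power figures considered when recruitment was stopped at 1,752 patients. For weight (SD 21.6 kg, 5 kg margin) it reports 90% power at 393 per group and 95% at 486. For events (25% against 16.25%, 413 per group) it reports 87.5%.

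**The concern.** A fixed split is the simplest way to protect two primary tests, but it discards alpha that could safely be reused. Once one outcome has succeeded at 2.5%, its share can pass to the other, which may then be tested at 5% with the family-wise error still held at 5%. If the overall claim needed both outcomes, no split would be needed at all.

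The trial was designed around a joint statement: weight loss not materially worse, and fewer serious complications. Showing both is therefore what matters most, and it is where the fixed split costs most. A split result is plausible too, since the protocol background expects somewhat less weight loss after SG and fewer bowel complications. With no stated rule for the overall claim, such a result could be presented either way after the data are seen.

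**Working it through.** **Inputs.** Levels: two-sided 2.5% (z = 2.241) from SAP 5.2, and two-sided 5% (z = 1.960) for comparison. Event rates: 13% for GBP (SAP 5.1) or 25% (appendix), each 35% lower with SG, giving 8.45% or 16.25%. Weight: SD 21.6 kg and margin 5 kg (appendix), true difference zero. Sample size: 413 per arm (appendix); or 1,752/2 = 876 per arm for events and 876 × 0.8 ≈ 701 per arm for weight, where 20% loss is an assumption borrowed from the appendix.

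**Step 1: reproduce the appendix.** For weight, n per group = 2(21.6/5)²(z + z_power)².

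| Level | 90% power | 95% power |
|---|---|---|
| two-sided 5% | 392.2, so 393 | 485.02, so 486 |
| two-sided 2.5% | 463.2, so 464 | 563.7, so 564 |

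The appendix figures of 393 and 486 match the 5% row exactly.

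For events, power = Φ[(p₁ − p₂ − z·SE₀)/SE₁]. At 413 per arm the difference is 0.0875, SE₀ = 0.02816 (pooled) and SE₁ = 0.02799.

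- At 5%: (0.0875 − 1.960 × 0.02816)/0.02799 = 1.154, power 87.6%. The appendix says 87.5%.
- At 2.5%: (0.0875 − 2.241 × 0.02816)/0.02799 = 0.871, power 80.8%.

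The appendix therefore used two-sided 5%, although it quotes the 2.5% level.

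**Step 2: power for each test alone, 413 per arm.** Call event power at 2.5% and 5% E₁ and E₂, and weight power W₁ and W₂. From step 1, E₁ = 0.808 and E₂ = 0.876. For weight, SE = 21.6 × √(2/413) = 1.503 and 5/1.503 = 3.326, so W₁ = Φ(3.326 − 2.241) = 0.861 and W₂ = Φ(3.326 − 1.960) = 0.914.

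**Step 3: Holm, assuming independent tests.** An outcome succeeds if it passes at 2.5%, or if it passes at 5% and the other passes at 2.5%.

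- Events: E₁ + (E₂ − E₁)W₁ = 0.808 + 0.068 × 0.861 = 0.866
- Weight: W₁ + (W₂ − W₁)E₁ = 0.861 + 0.053 × 0.808 = 0.904
- Both: E₁W₁ + (E₂ − E₁)W₁ + (W₂ − W₁)E₁ = 0.696 + 0.058 + 0.043 = 0.797
- At least one: 1 − (1 − E₁)(1 − W₁) = 0.973, the same as with the fixed split

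**Step 4: the same at the enrolment reached** (fixed split → Holm).

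| Scenario | Events | Weight | Both |
|---|---|---|---|
| 413 per arm, 25% rate | 80.8% → 86.6% | 86.1% → 90.4% | 69.6% → 79.7% |
| 876/701 per arm, 13% rate | 79.9% → 86.7% | 98.2% → 98.9% | 78.5% → 86.0% |
| 876/701 per arm, 25% rate | 98.9% → 99.5% | 98.2% → 99.1% | 97.1% → 98.6% |

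**Step 5: if both outcomes were required.** Each could be tested at the full 5%. At 413 per arm the power for both is 0.876 × 0.914 = 80.1%, barely above Holm's 79.7%. Without the independence assumption, power for both lies between 66.9% and 80.8% with the fixed split, and between 79.0% and 87.6% with two unsplit tests.

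**Step 6: error control.** The fixed split bounds family-wise error at 2.5% + 2.5% = 5%. Two unsplit 5% tests, with either counted as a success, would give 1 − 0.95² = 9.75% if independent. Some adjustment is therefore needed under the either-suffices reading.

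**The case against.** The fixed split is valid, its reason is stated, and it comes with matching intervals. Section 2 sets separate hypotheses, so a mixed result can be reported hypothesis by hypothesis. All of that stands; Holm is a better choice, not the correction of an error.

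Three stronger readings are tempting, and the documents do not support them.

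- *Power is lost even if one success is enough.* It is not. Holm's first step is the fixed split, so the chance of at least one success is identical (97.3% at 413 per arm).
- *The wording already requires both outcomes.* The co-primary label and the protocol's phrase lean that way, but the separate hypotheses and the split itself lean the other way. No rule is stated.
- *Recruitment was stopped on too little power.* The appendix used the wrong level, but its 413 comes from patients with 2-year weight data less 20%. SAP 5.4 expects nearly complete event coverage through registers, so 413 is not the event denominator. At 25% and 876 per arm, event power at two-sided 2.5% is 98.9%. For weight, the corrected 464 and 564 per group are both below 701.

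Two practical objections also stand. Because SAP 5.3 decides non-inferiority by the interval, using Holm while keeping only 97.5% intervals could produce an interval that crosses the margin beside a declared success. The change would also relax a threshold after recruitment closed and after pooled 2-year data had been used.

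**Conclusion.** The point holds as a cheap improvement. The fixed split controls error, but Holm is at least as powerful everywhere and strictly better for the second outcome and for showing both.

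The size depends on the event rate. In the appendix scenario the gain is about 6 points for events, 4 for weight and 10 for both. At the enrolment reached it is about 7 points for events if the 13% rate holds, and about 1.5 points or less on any measure if 25% holds. The appendix regards the higher rate as the better supported, so the gain may well be small.

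The figures assume independent tests, a comparison of proportions in place of the Cox model, a true weight difference of zero, a margin of 5 kg as in the appendix rather than the 5% of the SAP body, and 20% loss for weight. Whatever the correlation, Holm's power for each outcome lies between its 2.5% and 5% values.

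The appendix mismatch is a separate and firm finding: its figures hold at two-sided 5%. At the level in 5.2 they become 464 and 564 per group and about 81%. Holm does not correct this.

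**What to change.** Amend before the 5-year data are analysed, and date the amendment so that this is evident.

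1. In SAP 5.2, replace the fixed split with Holm across the two primary outcomes at a family-wise two-sided 5%: the smaller p-value is compared with 2.5% and, if it passes, the other with 5%. For weight, use the two-sided equivalent of the non-inferiority test.
2. State that an overall advantage for SG is claimed only if both outcomes succeed, and that otherwise each is reported on its own.
3. In 5.2 and 5.3, state that once the first outcome has passed at 2.5%, the second is judged with a 95% interval, so that the interval against the margin agrees with the test. Report 97.5% intervals for both as well.
4. In the appendix, restate the power at the level in 5.2: 464 and 564 per group for weight, and about 81% for events at 413 per group.

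The cost is a few sentences, with no new data or patients. There are two downsides. The interval level for the second outcome depends on the Holm step, and the threshold changes after recruitment closed. Dating the change before the 5-year analysis answers the second.

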### 5.3 Statistical analyses

Summary tables (descriptive statistics and frequency tables) will be provided for all baseline variables, outcome variables, and safety variables, as appropriate. Continuous variables will be summarized with descriptive statistics (n, mean, standard deviation, range, and median). Frequency counts and percentage of subjects within each category will be provided for categorical data.

Incidence of substantial adverse events will be analysed with time-to-event models. Time to first substantial adverse event (as defined in chapter 4 Study outcomes) from primary surgery will be recorded. Kaplan-Meier estimates of cumulative incidence of adverse events will be calculated in both treatment groups. Treatment effect will be calculated as a hazard ratio, together with corresponding confidence interval and p-value for the test of equal hazard ratio, from Cox proportional hazard regression model. The proportionality assumption of the Cox models will be evaluated graphically using "log-log" plots.

The primary conclusions will be based on a model which includes study centre as a covariate together with indicator for treatment. Explorative analyses will be conducted using sex, age, body mass index, smoking and diabetes at baseline as covariates.

For non-inferiority, the difference in weight loss between treatment groups and its confidence interval will be calculated and evaluated against the non-inferiority margin of 5%. The weight loss difference at 5-year follow-up will be estimated with a multilevel mixed-effect regression models utilizing body weight measurements at all available time points. This model takes into account the repeated measurements nested within persons over time. All randomized patients except those who have withdrawn their consent will be included in this analysis, independent of availability of body weight data during the follow-up. The primary conclusions will be based on a model which includes study center in addition to indicator for treatment.

For secondary outcomes, incidence of comorbidities during the follow-up will be evaluated with time-to-event models, and for continuous variables mixed-effect regression models will be used to evaluate differences between the treatment groups.

A priori defined subgroup analyses will be conducted by sex, age, diabetes state and baseline BMI for all outcomes. Age will be categorized in three groups (18-29; 30-45; > 45 years), and BMI as in two groups (<42 and  $\geq 42\text{kg/m}^2$ ).

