## Background

Laparoscopic Roux-en-Y gastric bypass (RYGB) has in recent years been the standard operation in Swedish bariatric surgery. The operation is well studied and we have a good idea of the expected result regarding weight, BMI, comorbidities, and it can be performed with a low complication rate. However, this does not mean that the surgical method is without challenges, and above all there is a small but important group of patients with prolonged morbidity after the procedure. Due to the bypassing of the duodenum and proximal jejunum, there is also a concern for long-term risk of various types of deficiency conditions.

Laparoscopic sleeve gastrectomy (SG) is a relatively recently introduced surgical method that in recent years has gained rapid and wide spread internationally and is currently the most commonly used obesity surgical technique in the United States. However, there are not results from long-term studies to the same extent as for RYGB. However, the reported data indicate good results regarding weight development and resolution of comorbidity up to a few years after the operation, although to a somewhat lesser extent compared to after RYGB. There are currently no long-term data presented for SG.

RYGB has been associated with a non-negligible risk of internal herniation with small bowel obstruction, which appears to affect at least 10% of patients operated on without closure of mesenteric defects, and despite closure a risk remains. This risk of internal herniation does not exist with SG. Another advantage of SG is that it avoids the problems with the Jejunojejunostomy (JJ), which seems to be part of the rare but difficult to treat morbidity after RYGB. There is also probably a slightly lower risk of vitamin and mineral deficiency because the duodenum and proximal jejunum are not bypassed. However, there are data that suggest that problems with gastro-oesophageal reflux may occur or worsen after SG and that continuous acid-suppressing treatment may be necessary. There are also indications that revisional surgery rates may be higher after SG, e.g. due to unsatisfactory weight development over time.

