## **Secondary outcome measures**

Secondary outcome measures include health economics, inpatient care, outpatient care, drug consumption, alcohol abuse, fractures, diabetes, cancer, mortality and quality of life. Secondary outcome measures are described in greater detail in the statistical analysis plan.

As a comparative measure of quality of life, patients will complete the EQ5D-5L, SF-36 and OP quality of life questionnaires at baseline, as well as at 1 year, 2 years and 5 years. In Norway, the validated quality of life questionnaires WRSM, IQOQOL, HADS, GSRS and GERDQ are also filled in. To look at quality of life related to alcohol, we also want to follow/analyze AUDIT and B-Peth, where those parameters are available.

The physical examinations (abdominal circumference, etc.) that are done and blood samples that are taken in the study at 1- and 2-year controls should take place in the time interval -1 month to +3 months around the target date. For the 5-year check-up, the time interval  $\pm$  6 months around the target date is accepted.

For data verification and completion, information regarding the bariatric surgery and background information can be retrieved from medical records.

The mandatory analyzes are vitamin D, P-Glucose and HbA1c. In Norway, a standard set of blood samples is taken in addition to the mandatory analyzes in SOReg.

We are planning subgroup analyzes regarding sex, age (18–29; 30–45; >45 years), BMI (<42 and >42kg/m^2 respectively, which is the median BMI in SOReg) and +/- type 2 diabetes.

Subgroup analysis regarding gallstone intervention is planned.

In addition to the clinical follow-up, we will, with the help of coordination between SOReg and other national registers (Medicines register (2005-), Patient register (inpatient care 1987-, Outpatient care 2001-); The Cancer Registry, Intensive Care Registry, National Diabetes Registry, Försäkringskassan's MiDAS register, the Swedish Tax Agency and other relevant national registers), get a good picture of the effect, safety and cost-effectiveness of each surgical method over a long follow-up period. In Norway, the corresponding national registers will be used (the Cancer Register, the Cause of Death Register, the Prescription Register, NPR data and data from Statistisk Sentralbyrå).

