|----------------------------------------------|-----------------------------|-----------------------------------------------------------------------------------------------------------------------------|
| Arterial cardiovascular events               | Baseline, 1, 2, and 5 years | Number of patients with Composite outcome including myocardial infarction, stroke and/or other occlusive arterial condition |
| Venous event                                 | Baseline, 1, 2, and 5 years | Number of patients with composite outcome including deep vein thrombosis, pulmonary emboli, and/or other venous events      |
| Diabetes requiring pharmacological treatment | Baseline, 1, 2, and 5 years | Development of diabetes measured as numbers of patients having a diabetes                                                   |

|                                                     |                             |                                                                                                                                  |
|-----------------------------------------------------|-----------------------------|----------------------------------------------------------------------------------------------------------------------------------|
|                                                     |                             | diagnosis with oral and/or injection treatment                                                                                   |
| Psychiatric morbidity                               | Baseline, 1, 2, and 5 years | Number of patients with pharmacological treatment for a psychiatric diagnosis                                                    |
| Hypertension                                        | 1, 2, and 5 years           | Number of patients with pharmacological treatment for                                                                            |
| Malignancy                                          | Baseline, 1, 2, and 5 years | Number of patients diagnosed with any type of malignancy
Data collected from Cancer registry                                  |
| Dyslipidaemia                                       | Baseline, 1, 2, and 5 years | Number of patients with oral lipid lowering treatment                                                                            |

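### Diabetes, dyslipidaemia, psychiatric morbidity and hypertension are counted as patients on treatment at set times, but the only planned model is time to new onset, with no at-risk set and no prespecified comparison of coming off treatment

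*Combined protocol and SAP*

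**What the plan says.** SAP version 5, section 4, secondary outcomes table:

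- Diabetes, at baseline, 1, 2 and 5 years: "Development of diabetes measured as numbers of patients having a diabetes" diagnosis with oral or injected treatment.
- Psychiatric morbidity, at the same times: "Number of patients with pharmacological treatment for a psychiatric diagnosis".
- Dyslipidaemia, at the same times: "Number of patients with oral lipid lowering treatment".
- Hypertension, at 1, 2 and 5 years only: "Number of patients with pharmacological treatment for" (the cell ends there in the text available to me, so I rest nothing on its exact wording).

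SAP section 5.3 gives binary comorbidities one inferential method: "For secondary outcomes, incidence of comorbidities during the follow-up will be evaluated with time-to-event models". Mixed-effect regression is reserved for continuous variables. The same section promises frequency tables for outcome variables and adds: "A priori defined subgroup analyses will be conducted by sex, age, diabetes state and baseline BMI for all outcomes".

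The protocol's Background says that data on sleeve gastrectomy show "good results regarding weight development and resolution of comorbidity up to a few years after the operation", to a somewhat lesser extent than after bypass. On laboratory tests, the protocol's section on secondary outcome measures says: "The mandatory analyzes are vitamin D, P-Glucose and HbA1c".

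**The concern.** A count of patients on treatment at a visit can rise through new disease and fall when patients come off treatment. A time-to-first-event model describes only the first of these, and only in patients who start without the condition.

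Patients treated at baseline are expected in this trial. The entry criteria do not remove patients treated for diabetes, hypertension or dyslipidaemia, and the only related psychiatric exclusion is unstable illness. Diabetes at baseline is itself a subgroup factor.

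An analyst following section 5.3 must therefore choose, without guidance, between two courses. Keeping treated patients means giving them an onset time that has no meaning. Dropping them means making no formal use of anyone who could come off treatment. Two competent analysts could report different hazard ratios from the same plan. Any later comparison of remission, or of the proportion on treatment, would be post hoc.

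**Working it through.** The plan states no power or sample size for these outcomes, so there is no figure to reproduce. The check sets the outcome table against the analysis section, then shows the scale under stated assumptions.

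**1. Outcome against model.**

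| Outcome | Measure in SAP section 4 | Times | Model in SAP section 5.3 |
|---|---|---|---|
| Diabetes | Treated diagnosis, labelled as development | Baseline, 1, 2, 5 years | Incidence, time to event |
| Dyslipidaemia | On lipid-lowering drug | Baseline, 1, 2, 5 years | Incidence, time to event |
| Psychiatric morbidity | On drug treatment | Baseline, 1, 2, 5 years | Incidence, time to event |
| Hypertension | On drug treatment | 1, 2, 5 years | Incidence, time to event |

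A baseline count makes sense for a prevalence measure or as a covariate. It cannot be an onset after surgery. Even the diabetes row, labelled as development, is measured as patients who have treated diabetes.

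**2. At-risk set.** Section 5.3 does not say whether patients treated at baseline enter the incidence model. Section 5.2 includes all randomised patients who have not withdrawn consent, which points to keeping them. For a patient already on treatment, no post-surgical date is a date of onset.

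**3. Subgroup rule.** Applying the four subgroup factors to all outcomes requires new-onset diabetes to be analysed among patients with diabetes at baseline. That quantity is undefined.

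**4. Are the data there?** Yes.

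- The baseline table of the perioperative analysis plan records drug treatment for diabetes, hypertension and dyslipidaemia (yes/no) and depression by diagnosis or medication.
- SAP section 3.4 links the prescribed drug and diabetes registers.
- HbA1c is mandatory under the protocol but does not appear in the SAP outcome table.

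**5. Scale (illustration).** Inputs from the documents: 1752 patients included and operated (SAP appendix) and 1:1 allocation (section 3.2), so 1752 / 2 = 876 per arm. Baseline prevalence p is an assumption, because the documents give none.

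- Treated at baseline, per arm: 876 × p.
- At risk of new onset, per arm: 876 × (1 − p).

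The last two columns give power to detect a difference between arms in the proportion off treatment among those treated at baseline. They use the two-proportion normal approximation at two-sided 5%; the proportions are assumed and everyone is taken as followed up.

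| p | Treated per arm | At risk per arm | Power, 60% v 50% | Power, 70% v 50% |
|---|---|---|---|---|
| 5% | 44 | 832 | 15% | 48% |
| 10% | 88 | 788 | 26% | 78% |
| 20% | 175 | 701 | 47% | 97% |
| 30% | 263 | 613 | 63% | >99% |
| 40% | 350 | 526 | 76% | >99% |

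The two sets of patients do not overlap. An onset model limited to the untreated uses no patient who could come off treatment, whatever the prevalence.

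**The case against.** Three arguments on the other side have force.

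**The trial can compare remission.** A reader might infer from section 5.3 that it cannot. The documents do not support that: treatment status at baseline and follow-up, register data and HbA1c are all available, and the promised frequency tables would show the counts by arm. What is missing is a prespecified comparison.

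**Resolution is not a stated objective.** A reader might infer that resolution is the effect of interest. It appears only as background. Where the documents name what they will follow, it is usually new disease: the protocol's Background speaks of diabetes development, and the SAP table of development of diabetes and of other comorbidities. The SAP Introduction adds that smaller trials found no major difference in resolution. The point therefore rests on the mismatch between table and model, not on a preference for remission.

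**Masking of a difference is not shown.** A reader might infer that counting treated patients as events would hide a real difference. Suppose new onset is 3% after sleeve and 2% after bypass, a ratio of 1.5, and every treated patient counts as an event. At p = 10% the ratio of cumulative risks becomes (0.10 + 0.90 × 0.03) / (0.10 + 0.90 × 0.02) = 0.127 / 0.118 = 1.08. But the SAP states no such event rule. Take treated status at 5 years instead, and assume 45% (sleeve) and 60% (bypass) of treated patients have come off treatment. At p = 15% the ratio is then (0.15 × 0.55 + 0.85 × 0.03) / (0.15 × 0.40 + 0.85 × 0.02) = 0.108 / 0.077 = 1.40. It is 1.41 at p = 10% and 1.40 at p = 20%. The result depends on a rule the plan leaves open, so no attenuation figure can be claimed.

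It can also be said that the protocol leaves detail to separate plans for each publication, and that the diabetes-by-diabetes cell is an obvious slip in a blanket sentence. Both are fair. But section 5.3 already fixes a method for these outcomes, and it is the wrong one for three on-treatment counts that include baseline. A later plan would have to depart from it.

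**Conclusion.** The point holds as a mismatch between outcome definition and planned model in SAP version 5. For these four medication-defined outcomes the at-risk set is undefined, no model compares the proportion on treatment, no remission comparison is prespecified, and one required subgroup analysis has no meaning.

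The size cannot be fixed from the documents. Under an assumed prevalence of 10-20%, 88-175 patients per arm would either have ill-defined onset times or drop out of formal analysis. The power figures are optimistic for any measure that needs a visit, since the SAP appendix itself assumes 20% loss between years 2 and 5. These are secondary outcomes with no power calculation; the primary conclusions on weight and substantial adverse events are not affected. The change is worth making because a better-matched analysis is available from data already collected.

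**What to change.** In SAP section 5.3, for diabetes, dyslipidaemia, psychiatric medication and hypertension:

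1. Compare the proportion on treatment at 1, 2 and 5 years with a logistic or mixed logistic model containing arm, centre and baseline treatment status. Add baseline to the hypertension row of the outcome table.
2. Restrict the time-to-event analysis of new onset to patients untreated at baseline. Report separately, by arm, the proportion off treatment among those treated at baseline.
3. Exempt new-onset diabetes from the diabetes-state subgroup analysis.

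As an optional supportive analysis, define diabetes status from treatment together with HbA1c, with the definition written down in advance. HbA1c will be missing for patients who do not attend, so the treatment-only result should stand beside it.

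The cost is SAP wording and modest extra analysis. No new data collection is needed.
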